### Primary hypotheses

Compared to usual care, Mitii™ training will achieve significantly greater gains in:Activities of daily living motor processing skills as indicated by an improvement of a minimum detectable change (MDC) of 0.5 logit scores on the Assessment of Motor and Process Skills (AMPS) immediately following training;Gross motor capacity assessed by 30 s repetition maximum (rep_max_) of functional strength exercises (MDC = ≥28 repetitions on composite score of three functional strength exercises)

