### Lower Limb (LL) functional strength

Thirty second repetition maximum (rep_max_) of functional strength exercises (including sit-to-stand, lateral step-ups and half-kneel to stand) will be tested according to published recommendations [93]:

Sit-to-stand: This test measures the ability of the participant to attain standing (from 90° knee flexion) as many times as possible in 30 s with arms free or placed on their hips and without support from the chair or their body. Height of the chair will be defined by the ability of the participant to attain 90° hip and knee flexion with feet flat on the floor. One repetition will be defined as each time the participant is within 15° of hip and knee extension, visually estimated by a physiotherapist.

Lateral Step-Up: The aim of this test is to perform as many step up repetitions onto a 20 cm step block as possible in 30 s. Participants will be asked to stand with the foot being tested on the step and the non-test leg on the floor, parallel and shoulder width apart. The participant then raises the non-test foot off the ground until the test leg has reached within 10° of knee extension (visually estimated) for the tested foot during the extension phase of the test. The non-test foot does not have to touch the step block. Repetitions will be counted each time the heel or toes of the foot not being tested touches the ground. Both legs will be tested with the dominant leg tested first.

Half-kneel to Stand: This activity tests the ability of participants to attain a stride stance through a half-kneel position without the use of arms for as many repetitions that can be completed in 30 s. The participant is placed in half-kneel with buttocks clear of the lower legs and floor. The participant will be instructed to assume a standing position within 15° of knee extension (visually estimated) and remain with their feet apart (one repetition). This is a slight adaptation to the original protocol where participants assumed a standing position with feet together. The dominant leg in front will be tested first and repeated for the non-dominant side.

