For each LL functional strength exercise participants will be given verbal and visual instructions as well as two practice repetitions prior to testing. The exercises will be assessed in the following order: (i) Sit-to-stand, (ii) Lateral step-up dominant, (iii) Lateral step-up non-dominant, (iv) Half-kneel to stand dominant and (v) Half-kneel to stand non-dominant and participants will be given verbal encouragement throughout. Participants will be given 180 s rests between exercises. If a participant cannot complete an exercise whilst performing the practice attempts, they will be assigned a score of 0 and will not proceed to testing.

Functional strength tests demonstrate acceptable inter-tester reliability (ICC= > 0.91; coefficient of variation (CV) 12.1-22.7 %) in 25 children with CP [93]. Reliability for each of these three tests was also strong (Lateral step up ICC = 0.94; Sit to stand ICC = 0.91; Half kneel to stand ICC = 0.93-0.96) [93]. Mean repetitions for each of the functional measures were as follows: (i) sit-to-stand was 14.4 (SD = 5.0; Standard error of measurement [SEM] = 1.5 reps; CV = 12.1 %), (ii) lateral step up left were 13.2 (SD = 10.5; SEM = 2.4 reps; CV = 17.8 %), (iii) Lateral step-up right was 12.6 (SD = 10.4; SEM = 2.6 reps; CV = 22.7 %), (iv) Half-kneel to stand left was 7.5 (SD = 5.5; SEM = 1.1 reps; CV = 28.6 %), (v) Half-kneel to stand right was 6.0 (SD = 5.3; SEM = 1.4 reps; CV = 39.9 %) [93].

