## Statistical analysis

### Sample size

The primary basis for sample size calculation for this study is adequate power (80 %) to detect a clinically important difference for the comparison between the functional effects of Mitii™ (as measured on the AMPS and rep_max_ of functional strength exercises) and usual care at the primary endpoint (20 weeks). This study examines a continuous response variable from matched pairs, waitlist control and immediate-intervention participants with one waitlist control per immediate intervention participant.

In a previous study of Mitii™ in children with unilateral CP (n = 102) the response within each group was normally distributed with SD 0.40 on the AMPS process subscales [49]. To detect a real changes in ADL processing abilities (0.30 units of greater) [92] between groups with 80 % power and α = 0.05, 29 children from each group are required to complete 20 week follow-up assessments.

For rep_max_ of functional strength exercises in a previous reliability study, the response within each subject group was normally distributed with a SD of five sit-to-stand repetitions [93]. If the clinically important difference between groups is four repetitions we will need 26 children from each group to complete 20 week follow-up assessments with, α = 0.05 [47].

Based on a previous RCT using 3T fMRI there were activation in the representative cortex for motor studies with good signal to noise ratio. Participant numbers will allow for some loss of information due to participant refusal (10 %) and scans where motion is a confounder (10 %). To detect fMRI changes between baseline to follow-up assessment (20 weeks) with 80 % power and a SD of 0.65, we will require 39 participants. If the supplementary motor area (SMA) is considered, given coefficients of variation (COV) for control subjects performing motor tasks (COV of 11 % in PM1 and 35 % in SMA, and activation signal of 1.5 %, we will be able to detect differences in percentage activation levels over time as small as 0.47.

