### Statistical analysis

Analysis will follow standard principles for RCTs. Primary and secondary outcomes will be assessed using two-group comparisons on all participants with evaluable data at 20 week follow-up assessments on an intention-to-treat basis. Statistical significance will be set at *p* < 0.05 for primary outcomes. Statistical significance for secondary outcomes will be defined separately for each suite of analyses prior to analyses being undertaken. Each significance level will be set to account for both type I and type II error rates due to the number of multiple comparisons. Validity of results will be checked using baseline and general descriptive information available for all eligible families. This includes comparing the key characteristics of families who completed the study with those who enrolled in the study but did not complete, and those who did not enrol. The primary outcome measures immediately post-intervention at 20 weeks will be AMPS and rep_max_ of functional strength exercises. Outcomes between treatment groups will be compared at follow-up using linear regression models, where treatment group (intervention or waitlist) and baseline score will be entered in as main effects. Secondary analyses will compare the outcomes between groups for physical activity, participation (CASE and CASP) and QOL (domains of Kidscreen-52).

For reproducibility studies (AMPS, physical activity capacity and performance measures and attention and executive functioning measures), units of variance will be assessed using an analysis of variance (ANOVA) model with Bland Altman Plots with 95 % limits of agreement (LOA). Intra-class correlation coefficients (model: 2-way mixed effects with absolute agreement) and 95 % confidence intervals will be calculated and interpreted as greater than 0.75 as excellent correlation, between 0.4 and 0.75 as adequate and less than 0.40, poor correlation [154]. The SEM will be calculated using [155]:$$ SEM= Standard\  Deviation\ (SD) \times \sqrt{\Big(1-ICC}\Big) $$

The MDC will be calculated using [155]:$$ MDC=SEM \times 1.96 \times \sqrt{2} $$

For attention and executive functioning measures, reliable change indexes (RCI) will be calculated using [156]:$$ RCI=\left( retestscore - initialscore\right)\div \left( standard\  error\  of\  difference,\  SDiff\right) $$

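### The 80 % power and 26 per group given for functional strength belong to sit-to-stand alone, not to the three-exercise composite named as the second primary outcome, and its two targets (28 and 4 repetitions) are not reconciled

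*Protocol article*

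**What the plan says.** The Primary hypotheses section expects greater gains in gross motor capacity on the 30-second repetition maximum, with the bracketed benchmark "MDC = ≥28 repetitions on composite score of three functional strength exercises". The Statistical analysis section repeats the outcome in general terms: "The primary outcome measures immediately post-intervention at 20 weeks will be AMPS and rep_max_ of functional strength exercises". The section on lower limb functional strength lists the exercises as "including sit-to-stand, lateral step-ups and half-kneel to stand". Step-up and half-kneel are each done on both legs, so five counts are recorded.

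The Sample size section opens by promising "adequate power (80 %) to detect a clinically important difference" on both the AMPS and the functional strength exercises. For the latter it says that "the response within each subject group was normally distributed with a SD of five sit-to-stand repetitions", and continues: "If the clinically important difference between groups is four repetitions we will need 26 children from each group".

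The lower limb section shows where the SD of 5 comes from: "sit-to-stand was 14.4 (SD = 5.0; Standard error of measurement [SEM] = 1.5 reps; CV = 12.1" %. The same paragraph gives much larger SDs for the lateral step-up. The article gives no SD for a composite and no rule for forming one.

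**The concern.** The variable that was sized is one component of the variable named in the hypothesis. A power statement holds only for the endpoint whose SD and difference went into it. If the composite is primary, one of the two primary outcomes has no power statement of its own.

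The same outcome also carries two targets on different scales: 28 repetitions in the hypothesis and 4 in the sample size. A reader of the results could not tell which one the trial was built around.

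**Working it through.** **Reproducing the plan's figure.** Two independent means, difference 4, SD 5, standardised difference 4/5 = 0.80, two-sided α = 0.05, 80 % power, 1:1. The t-based calculation gives 25.5, so 26 per group, with power 80.7 % at 26. Sidedness is not stated, but one-sided would give 20, so two-sided is the match. The arithmetic is right for sit-to-stand.

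**Inputs for the composite** (section on lower limb functional strength, a reliability study in 25 children with cerebral palsy):

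| Count | Mean | SD | SEM |
|---|---|---|---|
| Sit-to-stand | 14.4 | 5.0 | 1.5 |
| Lateral step-up left | 13.2 | 10.5 | 2.4 |
| Lateral step-up right | 12.6 | 10.4 | 2.6 |
| Half-kneel left | 7.5 | 5.5 | 1.1 |
| Half-kneel right | 6.0 | 5.3 | 1.4 |

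The means add to 53.7, the SDs to 36.7, the squared SDs to 301.75 and the SEMs to 9.0.

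**Composite SD.** Assume that the composite is the sum of the five counts, with a common correlation r between them. Then SD = √[(1 − r) × 301.75 + r × 36.7²]. A plain average over the five counts would have a mean of 53.7/5 = 10.7, so a benchmark of 28 points to a sum.

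| r | SD | Power for 4, n = 26 | Power for 28, n = 26 | Detectable at 80 %, n = 26 | Detectable at 80 %, n = 29 (0.75 SD) |
|---|---|---|---|---|---|
| 0 | 17.4 | 13 % | >99 % | 13.8 | 13.0 |
| 0.3 | 24.8 | 9 % | 98 % | 19.7 | 18.6 |
| 0.5 | 28.7 | 8 % | 93 % | 22.7 | 21.5 |
| 0.7 | 32.2 | 7 % | 87 % | 25.5 | 24.1 |
| 1 | 36.7 | 7 % | 77 % | 29.1 | 27.5 |

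n is per group; power is from the unadjusted two-sample t test. At 28 repetitions, power is exactly 80 % with 26 per group only if the SD happens to be about 35.3.

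**Other readings.** With one leg only (SDs 5.0, 10.5, 5.5) the SD is 12.9 to 21.0. Power at 26 per group is then 10 to 20 % for 4 repetitions and above 99 % for 28. If each exercise is tested singly, a 4-repetition difference at 26 per group has 27 to 28 % power for step-up and 73 to 76 % for half-kneel. The stated 80 % therefore holds for 4 repetitions on sit-to-stand only.

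**The figure of 28.** The Statistical analysis section gives MDC = SEM × 1.96 × √2 = 2.772 × SEM.

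- Independent errors: √(1.5² + 2.4² + 2.6² + 1.1² + 1.4²) = √17.94 = 4.24, so the MDC is 11.7.
- Fully correlated errors: 2.772 × 9.0 = 24.9.
- One leg only: 8.4 (left, independent) to 15.2 (right, fully correlated).

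An MDC of 28 needs a composite SEM of 28/2.772 = 10.1, which is more than the five SEMs added together. It is also 28/53.7 = 52 % of the summed reference mean.

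**The case against.** **Underpowering.** A reader might infer that the trial is too small. The documents do not support that. If 28 repetitions is the between-group difference, 26 per group gives 77 % to over 99 % power, and 30 per group gives 83 % in the worst case. Enrolment is set by the AMPS calculation (29 per group), not by this one. Power is low only for smaller composite differences, and the article plans for no specific one. Scaling 4/14.4 = 28 % up to the composite, about 14.9 repetitions, would be the reader's own construction.

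**28 as a pass mark.** A reader might also infer that the observed group difference must reach 28 for the hypothesis to succeed. No section says so. The test is a baseline-adjusted linear regression at p < 0.05, and by the article's formula an MDC describes measurement error in an individual's change.

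**Baseline adjustment.** The powers above ignore it, and adjustment would raise them. This stands, but the article gives no baseline-to-follow-up correlation. To bring even the smallest five-count SD (17.4) down to 5 would take a correlation of about 0.96, since √(1 − 0.96²) = 0.28 and 5/17.4 = 0.29.

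**Source of the 28.** The listed SEMs are inter-tester figures from children with cerebral palsy, and the 28 may come from elsewhere. This also stands: the 28 cannot be reproduced from the article, but that does not make it wrong. The hypothesis cites no source for it.

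None of this supplies a power statement for the composite.

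**Conclusion.** The point holds. The 80 % power and 26 per group are correct for a 4-repetition difference in sit-to-stand and do not apply to the composite in the hypothesis. Depending on which of the article's two targets is meant, power on the five-count sum at 26 per group is about 7 to 13 % or about 77 % to over 99 %. The benchmark of 28 lies above the 11.7 to 24.9 that the article's own SEMs and formula give.

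These ranges assume a five-count sum, a common non-negative correlation between counts, SDs carried over from the cerebral palsy study, and no baseline adjustment. The mismatch itself needs none of these assumptions, because it can be read directly from the two sections. The conclusion is that the stated power belongs to another variable and that two targets are unreconciled. It is not that the trial is underpowered.

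**What to change.** 1. In the Primary hypotheses section and the lower limb section, state how the composite is formed: which counts, one leg or both, and whether they are summed. The five-count sum used here is an assumption for the sponsor to confirm.
2. In the Sample size section, replace the sit-to-stand calculation with the composite difference detectable at the planned size, and show the SD assumption. At 29 per group this is 0.75 SD, or about 19 to 24 repetitions for a five-count sum with inter-test correlation 0.3 to 0.7.
3. Give the source of the 28, or restate it as an MDC that can be derived. Label it a measurement-error benchmark and do not use it as the sizing difference. The listed SEMs give only a range, so a single value needs a composite SEM or a stated error correlation.

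Alternatively, name sit-to-stand as the primary variable, keep 26 per group and make the composite secondary.

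Either route is a wording change and needs no extra children. The cost of the first is a less favourable stated detectable difference.

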### Secondary hypotheses

Compared to usual care, Mitii™ training will achieve significantly greater:Upper limb activity (unimanual and bimanual), as measured on the Jebsen-Taylor Test of Hand Function (JTTHF), MUUL and the Assisting Hand Assessment (AHA) [56];Lower limb gross motor capacity assessed using the Timed Up and Go (TUG) test, 6-min Walk Test (6MWT) and the High-Level Mobility Assessment Tool (HiMAT);Habitual physical activity (as measured on the ActiGraph® accelerometer) [57];Neurovascular (functional MRI) changes;Visual perception (visual discrimination, visual memory and visual sequential memory) measured on the Test of Visual Perception Skills (TVPS) [58];Executive functioning including information processing, attentional control, cognitive flexibility, goal setting, working memory and behavioural manifestations in everyday life as measured by subtests from the Delis-Kaplan Executive Function System (D-KEFS), the Wechsler Intelligence Scale for Children Fourth Edition (WISC-IV), the Comprehensive Trail Making Test (CTMT), Tower of London – Second Edition and the Behaviour Rating Inventory of Executive Function (BRIEF);Attention including performance on tasks of attention (TEA-Ch) and attention in everyday life as measured by parent rating (Conner’s 3);Psychological functioning as measured by the Strengths and Difficulties Questionnaire (SDQ);Performance and satisfaction with occupational performance goals using the COPM;Participation as measured by the Child and Adolescent Scale of Environment (CASE) and Child and Adolescent Scale of Participation (CASP);QOL on the domains of functioning and participation as measured on the Kidscreen-52;Parent reported functional abilities in self-care and daily activities (using the MobQues28) [59]

Finally, Mitii™ will be more cost-effective compared with usual care as shown by resource use and consequence based on function (AMPS) and QOL (Child Health Utility 9D (CHU-9D) [60] and Kidscreen-52 [61])

## Methods/design

### Ethics

Full ethical approval for this study has been obtained by the Medical Ethics Committee of The University of Queensland (2013000212) and The Royal Children’s Hospital, Brisbane (HREC/12/QRCH/222). Written and informed consent will be obtained from all participants and their parents or guardians before entering the trial. This trial has been registered with the Australian New Zealand Clinical Trials Registry (ACTRN12613000403730).

### Recruitment

Sixty children at least 12 months post an ABI, which was acquired ≥28 days post full term birth will be recruited into the Mitii™ study. To be eligible, participants must be:(i)Aged 8–16 years;(ii)Independently ambulant at Gross Motor Classification System (GMFCS) equivalent level I or II [62];(iii)Equivalent to a Manual Abilities Classification scale (MACs) of I to III [63];(iv)Co-operative and have sufficient cognitive understanding, visual and verbal abilities to perform the assessment and training tasks;(v)Classified with a brain injury which was acquired greater than 28 days after birth (based on the Australasian Rehabilitation Outcomes Centre impairment codes) [64]. For TBI, classified as mild complicated, moderate or severe brain injury;(vi)Able to participate in the study over a period of 12 months;(vii)Able to access the internet at home.

Children will be excluded if they have:(i)A degenerative or metabolic condition;(ii)Unstable epilepsy (i.e. frequent seizures not controlled by medication);(iii)Undergone any surgical or any medical intervention impacting on UL and LL function in the past six months as this will confound results.

All children will undergo a comprehensive screen by a rehabilitation consultant to confirm eligibility. Participants will be recruited through referral by treating clinical staff (paediatricians, neuropsychologists physiotherapists, occupational therapists and speech therapists) from the Queensland Paediatric Rehabilitation Service (QPRS), Brisbane, Australia who will ask families if they are willing to be contacted regarding potential involvement in the study. Following verbal consent, study personnel will provide participant information and seek informed consent. To assist recruitment, participants will be reimbursed for travel expenses and flexible times and locations for assessments will be arranged.

### Design

This study utilises a matched-pairs, randomised waitlist controlled trial (see Fig. 1 for CONSORT flow chart). A matched pairs design was chosen to minimise the risk of baseline between-group differences. A waitlist design ensures that all participants have access to this novel intervention and will facilitate recruitment into the study. Within each pair, each participant will be randomised into either:*Immediate intervention group:* Families return home with Mitii™ equipment and commence training immediately for 20 weeks and then Mitii™ is withdrawn; or*Waitlist delayed intervention (control) group:* Families continue care as usual for 20 weeks, return to Brisbane for a one day re-assessment and then return home with Mitii™ equipment to commence training for 20 weeks. Care as usual includes any therapies (for example, occupational therapy and physiotherapy) usually provided by public or private services and visits to their treating paediatrician or general practitioner. Information about each participant’s usual care during the study period will be gathered using a general study questionnaire. After re-assessment the participants (and their family) will receive the Mitii™ introduction and equipment ready to commence training.

**Fig. 1 Fig1:**
[figure not shown]
CONSORT Flow chart of the move it to improve it (Mitii™) study

To limit confounding variables during the immediate intervention period (baseline to 20 week follow up), it will be requested that participants delay any of the following concomitant treatments – casting, splinting, intramuscular botulinum toxin type A [BoNT-A] injections (to UL or LL) and surgery. Participants will be able to continue other usual care therapies. Participants who have received intramuscular BoNT-A prior to beginning the study will have their baseline assessments postponed until one month after their standard follow up has been completed (approximately 10–12 weeks post injection). Questionnaires will record the type, frequency and duration of any concurrent therapies provided by public and private services during the study for all participants.

### Randomisation

Participants will be matched in pairs according to age (18 month age bands) and intelligence quotient (IQ) of ≤80 or >80 (measured on the Wechsler Intelligence Scale for Children – Fourth Edition) [65]. Where available an IQ assessment which has been completed greater than 12 months post injury will be used, otherwise an IQ assessment will be completed prior to matching. Each member of the pair will then be randomly allocated either number “1” or “2” using a computer generated number table. Treatment allocations will be recorded on a piece of folded paper inside a sealed, opaque envelopes and opened (in consecutive order) by independent, non-study personnel. Allocations will read either: “1: Waitlist 2: Immediate”, or “1: Immediate 2: Waitlist”. After the randomisation process is complete, study personnel will be informed of group allocation and information packs will be sent out to families.

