**Methods/Design:**

Sixty independently ambulant children (30 in each group) at least 12 months post ABI will be recruited to participate in this trial. Children will be matched in pairs at baseline and randomly allocated to receive either 20 weeks of Mitii™ training (30 min per day, six days a week, with a potential total dose of 60 h) immediately, or be waitlisted for 20 weeks. Outcomes will be assessed at baseline, immediately post-intervention and at 20 weeks post-intervention. The primary outcomes will be the Assessment of Motor and Process Skills and 30 s repetition maximum of functional strength exercises (sit-to-stand, step-ups and half kneel to stand). Measures of body structure and functions, activity, participation and quality of life will assess the efficacy of Mitii™ across all domains of the International Classification of Functioning, Disability and Health framework. A subset of children will undertake three tesla (3T) magnetic resonance imaging scans to evaluate functional neurovascular changes, structural imaging, diffusion imaging and resting state functional connectivity before and after intervention.

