### Study procedure

To account for children’s varying abilities to attend and concentrate and, to mitigate fatigue the following scheduling strategies will be used to maximise data integrity during baseline and follow up assessments. Families will be contacted prior to baseline assessments to ascertain whether they feel their child will need one or two days to complete assessments. All participants will attend The University of Queensland, St Lucia campus for all assessments, minimising travel. Neuropsychological testing will be scheduled first as this requires most attention and concentration by participants. Regular breaks will be scheduled for participants between assessments as necessary at baseline and follow-up appointments. All primary outcome clinical assessments will be performed prior to Magnetic Resonance Imaging (MRI). Extra time will be allocated at the start and end of each day to manage any unforeseen complications which may arise (e.g. travel/time delays and fatigue issues). Participants in the immediate intervention group will spend an additional day for Mitii™ training and return home with Mitii™ equipment to begin the 20 weeks intervention. After baseline assessments (T0), the waitlist group will continue care as usual for 20 weeks. All participants will then return to The University of Queensland after 20 weeks for a one to two day re-assessment (T1). The waitlist group will spend an additional day for Mitii™ training before returning home with equipment to commence the intervention. For each participant data will be collected at Baseline (T0). The immediate intervention group will have follow up assessments conducted immediately post-training at 20 weeks (T1) and retention at 40 weeks post-baseline assessments (T2). The waitlist group will have a second baseline assessment at 20 weeks (T1), post-intervention at 40 weeks (T2) and retention of effects at 60 weeks post-baseline assessments (T3).

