#### Physical capacity and performance test-retest reproducibility and validity

Participants will have the option to participate in test-retest reproducibility study of rep_max_ of functional strength exercises, 6MWT, HiMAT and TUG test over two days at the testing facility during baseline (for the immediate group) or 20 week follow-up assessments (for the waitlist group). Accuracy between hand-timed and videos scores during the HiMAT and TUG test will also be investigated. Testing will be performed in the same order by the same physiotherapist.

Participants will also have the option to participate in the validation for the ActiGraph accelerometer as a measure of physical activity intensity in children and adolescents with an ABI. To validate the ActiGraph accelerometer, participants will be asked to return for one assessment day after they have completed the primary end-point (20 week assessment) for the RCT. For the validity protocol, participants will be asked to rest for a 5–10 min period and then conduct selected light, moderate and vigorous assessment tasks, interspersed with 5–10 min rest periods in a standardised manner. To finish, they will complete a 15 min Mitii™ training program adjusted for their individual capacity. These tasks will be performed whilst wearing an ActiGraph accelerometer, heart rate monitor and a portable indirect calorimeter (MetaMax®). For test-retest reproducibility of the ActiGraph accelerometer, participants will rest for five minutes before conducting selected light, moderate and vigorous assessment tasks, interspersed with 5 min rest period in a standardised manner over the baseline assessment and training days.

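### The text implies, and nothing shown prevents, release of allocation before T0, so the baseline AMPS and rep_max covariates may be scored with the arm known

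*Protocol article*

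**What the plan says.** All references are to the protocol article.

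- **Randomisation, inputs.** "Participants will be matched in pairs according to age (18 month age bands) and intelligence quotient (IQ) of ≤80 or >80". Where no suitable earlier IQ result exists, "otherwise an IQ assessment will be completed prior to matching". That is the only test placed before matching.
- **Randomisation, release.** Someone outside the study opens a sealed envelope. Its slip assigns one member of the pair to each arm. Then "study personnel will be informed of group allocation and information packs will be sent out to families".
- **Abstract, Methods/Design.** "Children will be matched in pairs at baseline and randomly allocated to receive either 20 weeks of Mitii™ training".
- **Study procedure.** "Participants in the immediate intervention group will spend an additional day for Mitii™ training and return home with Mitii™ equipment" to begin the intervention. For the other arm: "After baseline assessments (T0), the waitlist group will continue care as usual for 20 weeks".
- **Test-retest reproducibility.** The optional retest of rep_max and three other physical tests, spread over two days, takes place "during baseline (for the immediate group) or 20 week follow-up assessments (for the waitlist group").
- **Blinding.** Masked reading is stated for MRI and for the video ratings of AHA and MUUL. AMPS and rep_max are not listed. Elsewhere, AMPS is scored by an occupational therapist who also selects the tasks. For rep_max, a physiotherapist judges joint angles by eye and the child is encouraged during the test.
- **Statistical analysis.** The primary comparison at 20 weeks is a linear regression on treatment group and baseline score.

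**The concern.** A baseline covariate is safe in a randomised comparison when it is fixed before anyone can act on the allocation. If the T0 assessor, the child or the family already knows the arm, then effort, encouragement, task choice or scoring at T0 can differ between arms. Randomisation cannot remove such a difference, because it arises after allocation. The regression treats it as a true baseline imbalance and adjusts for it. Under-scoring at T0 in the immediate arm would then appear as benefit, and over-scoring would hide benefit. Both primary outcomes depend on the rater or on effort, so the route is plausible. The pair design adds a second route: once one child's arm is known, so is the partner's.

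**Working it through.** **1. Order of release and T0**

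| Step | What the text fixes | What it leaves open |
|---|---|---|
| Matching and randomising | Needs age band and IQ only | Whether T0 is already done |
| Release of allocation | Follows completion of randomisation | Timing against T0; whether T0 raters are among the personnel told |
| Information packs | Sent to families after randomisation | Whether they disclose the arm |
| Extra training day | Immediate arm only, at the T0 visit | Shows only that the arm is known by the end of the visit |
| Optional rep_max retest | At baseline for the immediate arm, at 20 weeks for the waitlist arm | The second test could fall on the training day, after the first T0 score |

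No row states that release precedes T0. Taken together they favour it: nothing measured at T0 is needed to randomise, posting packs fits families who have not yet attended, and the content of the T0 visit depends on arm. No row holds allocation back until T0 is scored.

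**2. The pair**

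One slip allocates both children. The first child to finish T0 must have an arm so that it is clear whether to stay for training. Opening the envelope then also determines the partner's arm. Unless the two are assessed together, at least one child per pair has T0 at a time when personnel can know the arm. The text does not say that pairs attend together, or that the partner's allocation is withheld.

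**3. Size**

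The plan's own sample sizes come first. A two-sample t-test with two-sided alpha 0.05 (sidedness assumed) and 80% power gives:

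- AMPS process, difference 0.30, SD 0.40: 28.9, so 29 per group, as stated.
- Sit-to-stand, difference 4, SD 5: 25.5, so 26 per group, as stated.

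This point does not change either figure.

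The adjusted effect is (difference in 20-week means) − slope × (difference in T0 means). If T0 in the immediate arm is wrong by −b, the effect shifts by +slope × b; if wrong by +b, by −slope × b. The documents give neither slope nor b, so both are assumed:

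| Slope | b (logit) | Shift (logit) | Share of 0.30 |
|---|---|---|---|
| 0.6 | 0.05 | 0.03 | 10% |
| 0.8 | 0.10 | 0.08 | 27% |
| 0.5 | 0.05 | 0.025 | 8% |
| 0.9 | 0.10 | 0.09 | 30% |

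The first two rows are the working range, and the last two widen the slope. As a guide to consequence, take 29 per group and treat 0.40 as the residual SD. The standard error is 0.40 × √(2/29) = 0.105. Shifts of 0.025 and 0.09 are then 0.24 and 0.86 standard errors, and the two-sided type I error would be about 5.7% and 13.7% instead of 5%. The same formula applies to rep_max, but no range is offered for it.

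**The case against.** The strongest objection is that the order is inferred. The release sentence says nothing about T0, and the abstract's reference to matching at baseline fits either order. The flow chart, where one would look for the order, is not shown. The Mitii intervention section places training after the assessments, so the arm need be known only when they end. The same test-retest section spreads the ActiGraph retest across the assessment and training days, so the rep_max retest may also follow the first T0 score. All of this stands. A reader might infer that allocation definitely is released before T0, and the documents do not support that.

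Two further inferences are tempting and also go too far. One is that families learn from the packs that they are waitlisted and drop out before T0. The packs are not said to reveal the arm, and such dropout is a possible risk that the text does not show. The other is that the AMPS result will be inflated by 10 to 27%. That range is the product of assumed inputs, and the error could as well run the other way and mask benefit.

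It can also be said that unmasked scoring at 20 weeks matters more, since error there enters the effect in full while T0 error is scaled by the slope. That is correct, but it is a separate issue and does not protect the T0 score.

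What remains is that the article itself describes the release step, the arm-dependent visit and the scope of masking. Read together, they leave the baseline covariate exposed.

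**Conclusion.** The point holds as an unprotected step, not as a demonstrated fault. The text implies, without stating, that allocation is released before T0, and nothing in the text shown prevents it. With no masking stated for AMPS or rep_max, the baseline scores in the primary model may be taken with the arm known. The partner's arm is exposed as well unless the pair is assessed together.

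The size is unknown. The illustrative AMPS shift of 0.03 to 0.08 logit assumes a slope of 0.6 to 0.8 and a differential T0 error of 0.05 to 0.10 logit, with no fixed direction. It shows that a small error would not be negligible against a 0.30 target with 29 per group. It does not show that such an error will occur. The change is a cheap improvement worth making.

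**What to change.** State in the Randomisation section that the independent person who opens the envelopes releases allocation only after T0 AMPS and rep_max have been scored.

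- Where the two members of a pair attend together, hold release until both have been scored.
- Where they do not, keep the partner's allocation from the T0 assessors until that child's T0 is scored.
- Keep any information pack sent before T0 neutral as to arm.

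The cost is a change of wording plus some logistics. Families must keep one possible extra day free at T0 before knowing whether they need it, and trainers and equipment must be provisionally available for that day. The second safeguard is the weaker one, because it relies on assessors not learning the arm of a child whose partner may already have stayed for training. No sample size changes. Scoring at 20 weeks is left as it is and needs its own remedy.
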